### Sampling

The primary outcome data will be collected on a sample of patients from only one ward per group due to resource constraints. Given that the median length of stay in the hospital is only 4–5 days, and our requirement is to collect weight data over at least a 1 week period, we will purposively sample a ward that is most likely to care for patients who have a length of stay in excess of 7 days. To further minimise the number of patients for whom a weight on admission is collected but who are discharged before 7 days, patients with Diagnostic Related Groups (DRGs) known to have longer than average length of stay will be targeted. The following patients will be excluded from body mass measurement: those undergoing palliation or expected to die within a month, those undergoing amputation or surgical removal of large tumours, those admitted directly to the intensive care unit or with stays in intensive care of more than 3 weeks. A total of 20 patients for each of four wards will be weighed on each of five measurement periods, resulting in a total sample size of 400. Whilst it was desirable to include either more wards or more patients per ward (see power calculations in Analysis) in the sample, resource constraints limited the final sample size available for analysis. Given the size of the wards (typically 20–24 patients each) it is anticipated that it may take repeated weekly visits over an entire month to reach a total sample of 20 patients with body weight measurements for each sampling period. Patients whose length of stay exceeds 14 days will be weighed at day 14 and day 21 to allow calculation of change in weight over the first, second and third weeks of their admission. The second and third week data will both be analysed separately.

Secondary outcomes and hospital process measures will only be collected from the records of patients included in the primary outcome sample, described above. Written consent to weigh patients will not be sought because it is routine practice and part of usual care in the hospital.

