**Methods/Design:**

A pragmatic stepped wedge randomised cluster trial with repeated cross section design will be conducted. The unit of randomisation is the ward, with allocation by a random numbers table. Four groups of wards (n = 6 for three groups, n = 7 for one group) will be randomly allocated to each intervention time point over the trial. Two trained local facilitators (a nurse and dietitian for each group) will introduce the intervention. The primary outcome measure is change in patient’s body weight, secondary patient outcomes are: length of stay, all-cause mortality, discharge destinations, readmission rates and ED presentations. Patient outcomes will be measured on one ward per group, with 20 patients measured per ward per time period by an unblinded researcher. Including baseline, measurements will be conducted at five time periods. Staff perspectives on the context of care will be measured with the Alberta Context Tool.

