### Specific aims and hypotheses

The study seeks to address four key questions. Firstly, does a multifaceted intervention incorporating a malnutrition screening tool, nutritional supplements and red trays implemented in a hospital improve outcomes for older, at risk patients? Secondly, does the intervention have any impact on staff-related factors (eg receptivity to evidence, staff behaviour and actions) and hospital processes related to nutrition? Thirdly, does the model of facilitated implementation of nutritional evidence support frontline staff to provide evidence-base care? Fourthly, what are the implications for implementing evidence on nutrition within an organisation in terms of successful strategies, sustainability, and study design?

The whole evaluation of the implementation, which will include a stepped wedge design and a full process evaluation of facilitator and staff experiences, will add to existing strategies for implementing nutritional evidence into practice, thereby addressing questions 3 and 4. The following hypotheses that are most pertinent to this study protocol relate to questions 1 and 2 only:

1.1 The multifaceted nutrition intervention will improve outcomes (e.g. prevent nutritional decline, reduce mortality, readmission rates) for older, at risk patients.

2.1 The multifaceted nutrition intervention will improve staff-related outcomes (e.g. receptivity to evidence, staff behaviour).

2.2 The multifaceted nutrition intervention will improve hospital processes related to patient nutrition (e.g. weighing patients, screening patients, documentation).

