### Inclusion and exclusion criteria

Critical care areas will be excluded from the study, all remaining 25 wards will be allocated to one of the four stepped wedge groups. Otherwise, there are no exclusion criteria for implementing the intervention-all nursing staff and patients on the wards will be eligible to be exposed to the intervention. The patients will all be over 18 years of age with no upper age limitation.

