### Outcomes

The primary patient outcome measure will be the rate of change in body mass and body mass index over weekly periods from admission to discharge. Body mass (kg) will be measured to the nearest 0.1 kg, between 0800 and 1200 and post bladder voiding. Depending on patient mobility this may require a standing, sitting, bed or sling weighing machine. Patient’s height (cm) will be measured to the nearest 0.1 cm using a stadiometer or predicted from measured ulna length depending on patient mobility. Body mass index (kg/m^2^) is calculated as body weight divided by height squared. The body mass data will be collected by a researcher (LL), who is not blinded to the randomisation schedule.

Secondary patient outcome measures will include: length of stay, all cause mortality, discharge destination (to a higher, lower or equivalent level of care), number and duration of re-admissions (defined as an unplanned admission within 28 days of discharge related to the primary admission [62] (3, 6, 12 months post-discharge), and number of Emergency Department (ED) presentations (3, 6, 12 months post-discharge). The re-admission and ED presentations data will be collected from across all five major public hospitals in the metropolitan region using the State’s patient record systems, which will also provide length of stay, discharge destination and mortality, cross-referenced with State death registries. The collector of the secondary patient outcome data will be blinded to the randomisation schedule.

The staff-related outcome is nurse perspectives of context of care as assessed by administration of the Alberta Context Tool (ACT) [63,64] before the intervention.

Hospital process-related outcomes include: compliance to using the MUST tool on all patients, compliance to using additional food supplements when indicated, compliance to using the red tray system when indicated and compliance to documenting patient’s foods and fluids intake by nurses. The hospital process measures will be obtained through medical record review.

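### Different patients are weighed in each period, but no fixed rule decides which ones, and the all-adult sample does not match the older, at-risk patients of hypothesis 1.1

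*Protocol article*

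**What the plan says.** All references are to the protocol article.

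- **Design.** The section on the stepped wedge trial describes a repeated cross-section, with different patients in each ward at each sampling period.
- **Choice of ward.** Under Sampling, one ward per group is measured: "we will purposively sample a ward that is most likely to care for patients" with stays beyond seven days.
- **Choice of patient.** Within that ward, "patients with Diagnostic Related Groups (DRGs) known to have longer than average length of stay will be targeted". The section expects that "it may take repeated weekly visits over an entire month to reach a total sample of 20 patients". It adds that "Written consent to weigh patients will not be sought", because weighing is usual care.
- **Who measures.** The Abstract describes the measurement as "with 20 patients measured per ward per time period by an unblinded researcher". Outcomes says that body mass is collected by a researcher "who is not blinded to the randomisation schedule". The collector of secondary outcomes is blinded, but Sampling takes secondary and process outcomes only from the patients already in the weighed sample.
- **Target population.** The first research question is: "does a multifaceted intervention incorporating a malnutrition screening tool, nutritional supplements and red trays implemented in a hospital improve outcomes for older, at risk patients". Hypothesis 1.1 names the same population.
- **Sampled population.** Under Inclusion and exclusion criteria: "The patients will all be over 18 years of age with no upper age limitation". The exclusions from weighing concern palliation or expected death, amputation or large tumour surgery, and intensive care. None concerns older age or nutritional risk.
- **Acknowledged limits.** The Discussion says that the targeted sample limits power and generalisability.

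**The concern.** Ward randomisation fixes when each ward changes phase. It does not make the patients weighed before and after the change alike, because they are different people. Only the sampling rule can do that. A rule that names a target group and a quota, but no order of entry, leaves room for the case mix to drift with phase. The collector knows the phase. By author code, that collector is also one of the clinicians in the partnership formed to help facilitate and evaluate the intervention. With no separate consent step, being weighed amounts to being included.

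A drift of this kind would bias the primary comparison. Blinding the secondary-outcome collector would not remove it from the secondary outcomes, because the patients are the same.

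The second issue is the question being answered. Supplements are meant for patients identified as at risk, and hypothesis 1.1 is about older patients at risk, yet any adult in a long-stay DRG can enter the sample. A result in that sample, positive or null, is not a direct test of hypothesis 1.1.

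**Working it through.** **1. What determines inclusion.** The article states:

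| Step | Stated rule |
|---|---|
| Ward | purposive, on expected stay |
| Patient | long-stay DRG, minus the listed exclusions |
| Order of entry | repeated weekly visits until 20 are reached |
| Consent to weighing | no written consent |
| Collector's knowledge of phase | knows the schedule |

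No consecutive, random or list-based order is given, so two people applying these rules could assemble different sets of 20.

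**2. Population.** The hypothesis is about older patients at risk. The sample is adults over 18 in long-stay DRGs. The Setting section reports internal audits with up to half of patients at risk, so part of the sample may lie outside the hypothesis. That share is not known for the targeted wards.

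**3. Reproducing the plan's power.** Inputs from Analysis: 4 wards (I), 5 periods (T), 20 per cell (n), baseline prevalence 0.267, tau 0.056. Alpha is not stated, so two-sided 0.05 is assumed. The Hussey and Hughes variance is

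Var = I·s²·(s² + T·τ²) / [(I·U − W)·s² + (U² + I·T·U − T·W − I·V)·τ²]

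- s² = 0.267 × 0.733 / 20 = 0.009786; τ² = 0.003136
- From Table 1: U = 10, W = 0+1+4+9+16 = 30, V = 16+9+4+1 = 30
- Numerator: 4 × 0.009786 × (0.009786 + 0.01568) = 0.000997
- Denominator: 10 × 0.009786 + 30 × 0.003136 = 0.1919
- Var = 0.00519, SE = 0.0721

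Power for 26.7% to 6.5%: Φ(0.202/0.0721 − 1.96) = 0.80 (stated 80%). For 26.7% to 16.5%: Φ(0.102/0.0721 − 1.96) = 0.29 (stated 29%). Both reproduce.

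**4. Illustration of a phase-related shift.** Suppose there is no true effect and case mix moves intervention-phase prevalence by b. The two-sided type I error is Φ(−1.96 + b/SE) + Φ(−1.96 − b/SE):

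| b | type I error |
|---|---|
| 0 | 5.0% |
| 2 points | 5.9% |
| 5 points | 10.7% |
| 10 points | 28.4% |

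Five points is one patient in 20 (0.05 × 20 = 1) in every intervention cell. The values of b are assumptions; the documents supply none.

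**5. Power of an at-risk subset.** Assume half the sample, so 10 per cell. Then s² = 0.01957, Var = 4 × 0.01957 × 0.03525 / (0.1957 + 0.0941) = 0.00952 and SE = 0.0976. Power for 10.2 points is Φ(0.102/0.0976 − 1.96), about 18%.

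**The case against.** **Discretion is limited.** There is a DRG criterion with a stated reason (avoiding discharge before day 7) and a list of exclusions. On wards of 20–24 beds, needing up to a month to reach 20 suggests that eligible patients are scarce. This narrows the room for choice but does not remove it, because consecutive entry is not promised.

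**Ward choice is mainly about generalisability.** The same four wards are measured throughout and each serves as its own control. This stands. The article does not say whether the measured wards are chosen before or after allocation, so the weight of the point falls on selection within the ward.

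**The article is a condensed document.** A log of unmeasured patients and the model covariates could sit in a fuller protocol or SAP. Their absence is not counted as an error here. The point rests on the targeting rule that the article does state.

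**The results are described as preliminary.** The Discussion concedes low power and purposive sampling, and notes that clustering has implications for blinding and recruitment. It does not address bias between phases.

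A reader might also infer more than the documents support:

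- *That the unblinded researcher picks the patients.* The text says this researcher collects the weights. It does not say who does the targeting.
- *That there is no age criterion.* A minimum of over 18 applies; what is missing is an older-age criterion.
- *That a biased sample could never be detected.* Admission BMI is measured, so shifts in measured case mix could be seen. Shifts in unmeasured factors could not.
- *That the planned effect should be halved because about half of patients are at risk.* The 26.7% and 16.5% in Analysis are prevalences among measured patients, so 10.2 points is already a whole-sample effect. The audit figure is an upper one, not specific to the measured wards, and benefit confined to at-risk patients is an assumption.

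**Conclusion.** The point holds in two parts. First, in a design with new patients each period, the stated rule does not fix which eligible patients are weighed, and the collector of the primary outcome knows the phase. The comparison between phases is therefore open to selection bias, which the acknowledged limits do not cover. This is an exposure to bias, not evidence that bias occurred. Second, the sampled population is wider than that of question 1 and hypothesis 1.1.

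The documents give no size for either problem. The rise to about 11% for a 5-point shift rests on an assumed shift in every intervention cell, an assumed two-sided 5% level, and the binary weight-loss prevalence used for power. The primary outcome in Outcomes is a rate of change in body mass and BMI, so the figure shows scale only. A 2-point shift would do little harm (5.9%).

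**What to change.** 1. Set the DRG list and the measured wards before allocation is known. Ranking the wards by expected stay in advance, and measuring the top-ranked ward in each group, would do this without altering the allocation procedure.
2. In each period, take consecutive eligible admissions from the admission list until 20 are reached, and log eligible patients who were not measured.
3. Restate hypothesis 1.1 as concerning adult long-stay patients. Pre-specify the older at-risk subset as a secondary analysis and acknowledge its low power (about 18% for 10.2 points if half the sample qualifies). Define the subset the same way in both phases, from the researcher's own admission BMI and age. The ward's MUST result is unsuitable because MUST is part of the intervention.
4. Adjust the primary model for admission BMI and age. This deals with measured case-mix shifts only.

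The cost is protocol wording, a log and the recording of age. The researcher and the total of 400 patients stay the same. The downside is less freedom in choosing patients and possibly slower accrual to 20 per cell.

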The stepped wedge allows all clusters to receive the intervention. Further, unlike a conventional crossover trial, no clusters are removed from the intervention, which is ethically preferable if there is the prior belief that the intervention should result in benefits for the patient population [54,55,59]. The design also allows for a staged implementation, which is particularly beneficial if there are logistical, practical or financial limitations to rolling out an intervention at all sites in one time period [59]. The design supports evidence implementation in complex, changeable environments because the staged implementation allows improvements to be made to the intervention, for example training materials can be updated to accommodate feedback from participants. Analysis of stepped wedge trials can adjust for possible temporal trends in the effectiveness of the intervention, and the design reduces the impact of intra-cluster correlations on power because each group acts as its own control [54]. A disadvantage of the design is the need for data collection from all units at each sampling period, and potential lengthening of the trial to allow sequential roll out of the intervention across all groups [54]. These attributes support the use of routinely collected hospital administrative data as outcomes of stepped wedge trials.

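### Tying secondary outcomes to the weighed sample would, on the natural reading, drop patients who leave or die before day 7, and it leaves 21 of 25 randomised wards out of record-based outcomes without a stated reason

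*Protocol article*

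**What the plan says.** The Sampling section fixes the source of the secondary data: "Secondary outcomes and hospital process measures will only be collected from the records of patients included in the primary outcome sample, described above". The primary outcome sample is narrow in three ways.

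- **Wards.** "The primary outcome data will be collected on a sample of patients from only one ward per group due to resource constraints". The ward is not drawn at random: "we will purposively sample a ward that is most likely to care for patients who have a length of stay in excess of 7 days". Under Inclusion and exclusion criteria, however, "all remaining 25 wards will be allocated to one of the four stepped wedge groups".
- **Patients.** Diagnosis groups with long expected stays are targeted. Patients receiving palliation or expected to die within a month are excluded from weighing.
- **Observation time.** The section states that "our requirement is to collect weight data over at least a 1 week period", and it treats discharge before day 7 after an admission weight as something to be minimised.

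The Outcomes section lists length of stay, all-cause mortality, discharge destination, readmissions and emergency presentations as secondary. Readmissions and emergency presentations come from the State's patient record systems, "which will also provide length of stay, discharge destination and mortality, cross-referenced with State death registries". The Stepped wedge trial section comments on the design's need for data from all units in every period and concludes: "These attributes support the use of routinely collected hospital administrative data as outcomes of stepped wedge trials".

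**The concern.** There are two separate issues.

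First, a sample defined by having a one-week weight is defined by something that happens after the patient has been exposed to control or intervention care. For weight change that is hard to avoid. For length of stay and mortality it matters more, because the condition (still in hospital and alive at day 7) is part of the outcome. Stays under a week would be invisible, first-week deaths would not be counted, and if the intervention changed who reaches day 7, the two phases would compare differently selected patients.

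Second, the Discussion justifies the small sample by the poor quality of routine body-weight data, which made prospective weighing necessary. That reason applies to weight. It does not apply to outcomes that the plan already takes from record systems and death registries. Hypothesis 1.1 names mortality and readmission, so these outcomes are not incidental.

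**Working it through.** **1. Is a day-7 condition in the plan?** Three statements bear on it. Sampling requires a week of weight data. Outcomes defines the primary measure as change over weekly periods from admission to discharge. Analysis bases power on first-week weight loss with 20 patients per ward-period, 400 in total. A patient who leaves or dies before day 7 cannot supply that measure, and no sentence keeps such a patient in the secondary-outcome sample. Exclusion is therefore the natural reading. It is not the only one, because Sampling also foresees patients with an admission weight and no day-7 weight and does not say what becomes of their records.

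**2. The plan's own power figures.** Inputs from Analysis: control rate 0.267, between-cluster SD τ = 0.056, 20 patients per cluster-period, T = 5 periods. Assumed: two-sided 5% level, which is not stated. With σ² = 0.267 × 0.733 / 20 = 0.009786 and τ² = 0.003136, the closed-form stepped wedge variance is

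Var = Iσ²(σ² + Tτ²) / [(IU − W)σ² + (U² + ITU − TW − IV)τ²],

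where I is the number of clusters, U the number of intervention cluster-periods, W the sum of squared period totals and V the sum of squared cluster totals of those cells.

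- *Four wards:* I = 4, U = 10, W = 30, V = 30. Var = 0.000997 / (10 × 0.009786 + 30 × 0.003136) = 0.00519, so SE = 0.0721. Power = Φ(0.202/0.0721 − 1.96) = 80% for a fall to 6.5%, and Φ(0.102/0.0721 − 1.96) = 29% for a fall to 16.5%. Both match the protocol.
- *All 25 wards, 20 per ward-period:* U = 61, W = 1129, V = 181. Var = 0.00623 / (396 × 0.009786 + 1176 × 0.003136) = 0.000824, so SE = 0.0287. Power for the fall to 16.5% is Φ(0.102/0.0287 − 1.96) = 94%.

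The protocol gives 69% for this 25-ward design. That figure does not reproduce with the formula that returns its four-ward figures. This is a separate matter, but a reader comparing the two should know of it.

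**3. Wards used.** 25 − 4 = 21 wards (84%) are randomised and receive the intervention but supply no patient outcomes.

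**4. What truncation would do to length of stay.** The protocol gives only a hospital-wide median stay of 4-5 days. Assumed: a uniform true 10% cut, and an exponential or log-normal stay (log-SD s from 0.7 to 1.1). Among stays above 7 days:

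- Exponential with mean μ = median / ln 2: ratio of means = (7 + 0.9μ) / (7 + μ). At a median of 4.5, μ = 6.49 and the ratio is 12.84 / 13.49 = 0.952.
- Log-normal with median m: mean above 7 = m·exp(s²/2)·Φ(d + s)/Φ(d), with d = ln(m/7)/s. The ratio compares 0.9m with m.

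| Assumed median (days) | Share above 7 days, exponential | Apparent cut, exponential | Apparent cut, log-normal |
|---|---|---|---|
| 4 | 30% | 4.5% | 2.8-3.8% |
| 4.5 | 34% | 4.8% | 3.1-4.0% |
| 5 | 38% | 5.1% | 3.3-4.3% |
| 7 | 50% | 5.9% | 4.4-5.0% |
| 10 | 62% | 6.7% | 5.8-5.9% |
| 12 | 67% | 7.1% | 6.4-6.5% |

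The first three rows use the hospital-wide median; the last three are assumed medians for the chosen wards. Membership also shifts with the effect: under the exponential model the share passing day 7 falls from 34% to 30% at a median of 4.5, and from 62% to 58% at a median of 10.

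**The case against.** The strongest reply is that patients are not selected on the outcome at all. Wards and diagnosis groups are chosen for *likely* long stays, by the same rule in both phases. That stands: such targeting restricts generalisability, which the Discussion admits, and does not by itself bias the comparison. A reader might infer that the plan picks patients because they stayed seven days. The text does not say so.

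Second, the loss of early leavers is inferred. This also stands, and it is why the point is conditional. If the intention is to keep them, one sentence settles the matter.

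Third, differential selection needs an intervention effect on stay or early death, and the Background reports no significant reduction in mean stay from supplements. That makes a large shift less likely. However, supplements are one of three components, and length of stay is listed as an outcome precisely because an effect is thought possible.

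Fourth, the truncation argument bears on length of stay and mortality. No comparable mechanism is shown for discharge destination or readmission. This stands; for those outcomes the point is the unused wards.

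Fifth, the study question concerns older, at-risk patients, so all adult admissions would add short stays with little exposure. Readmissions must also be unplanned and related to the first admission, which may need case review. Both are fair and shape the fix. Neither explains why length of stay or mortality should come only from weighed patients.

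**Conclusion.** The point holds as a recommendation on secondary outcomes in a study that describes its results as preliminary. On the natural reading of the sampling rule, length of stay would be truncated at about 7 days and first-week deaths omitted, with inclusion depending on a post-exposure event. If so, an assumed 10% cut in stay would show as about 3-5% at the hospital-wide median, or about 4-7% at assumed ward medians of 7-12 days. The second range is probably nearer for the chosen wards. Both depend on assumed distributions and a uniform effect.

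The stated weighing constraint does not justify omitting 21 of 25 randomised wards from record-based outcomes. The fall in SE from 0.072 to 0.029 only illustrates the possible gain: it borrows the weight-loss rate and τ, and the protocol gives no event rates or SDs for the secondary outcomes. A reader might infer that bias in these outcomes is established, or that their power is known to be low by this amount. The document supports neither statement.

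**What to change.** 1. **Define the secondary-outcome sample at enrolment.** State that it comprises all patients enrolled at the admission weight, whether or not they reach a day-7 weight, analysed by randomised step. This removes the conditioning on a later event and needs no further measurement on patients.

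2. **Add a 25-ward analysis of record-based outcomes.** For length of stay, all-cause mortality and emergency presentations, and for unplanned readmission and discharge destination where they are coded, analyse adult admissions to all 25 randomised wards in each measurement period. Attribute each to the ward of admission and apply no length-of-stay condition. A subgroup of older or long-stay-diagnosis patients, defined as far as possible by what is known at admission, keeps the link to the target population.

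3. **Leave the labour-intensive items where they are.** Chart-review process measures, and any readmission judgement needing case review, can stay in the 400.

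The cost lies in item 2: a larger data extract, and dilution by short stays in the overall analysis, which the subgroup partly offsets.
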